| Statistical analysis                   | 
The analyses will follow the intention to treat principle. The primary outcome will be a comparison of the viral load logarithm decay rates via RT-PCR to SARS-CoV-2 in 10 days between treatment groups compared to control. A linear mixed model will be used, assuming random intercept and slope for patients. The viral load measurements will be performed 5 and 10 days after randomization.
 
If the RT-PCR exam is not performed for any reason, imputation will be performed using only an estimate via the chain equation method using the mice package. We chose to perform the primary outcome assessment based on multiple imputation methods to correct any viral load values due to loss of information due to mortality, however, based on data by [name] et al. (2020), the expected mortality during the period of exam collection is minimal (<3%).
 |
| Data and security monitoring committee | 
An external and independent data monitoring committee (DMC) will assess safety outcomes and primary outcomes when 60 patients reach the primary assessment of the study outcome. The DMC will
                                                                                                                                                                                                                                                                                                                                                                                                                                                                                                                                                                                                                                                                                              |

|  |                                                                                                    |
|--|----------------------------------------------------------------------------------------------------|
|  | consider safety events to provide a recommendation to continue inclusion or discontinue the study. |
|--|----------------------------------------------------------------------------------------------------|

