#### *3.8.1 Day 1 - baseline*

- Eligibility Check;
- Informed Consent Process and signature of the Form;
- Randomization;
- Collect demographic and baseline data;
- Collection of laboratory tests: complete blood count (CBC), urea, creatinine, alkaline phosphatase, gamma-GT, aspartate aminotransferase, alanine aminotransferase, direct and indirect

bilirubin, C-reactive protein, prothrombin time with RNI, activated partial thromboplastin time, fibrinogen, , sodium and potassium;

- Collection of nasopharyngeal swabs for SARS-CoV-2;
- Collection of urine for pregnancy test (in the case of women of childbearing age);
- Dispensing and guiding the use of study medication.

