### *3.10.8 COVID-19 negative confirmatory exam*

Patients who are included in the study based on the results of rapid tests such as GeneXpert Cepheid® (ANVISA Registration Number 81062710039) or commercially analogous, or rapid Antigen test (COVID - 19 Ag ECO Test - ANVISA Registration Number 80954880133) who have a negative laboratory diagnosis by RT-PCR for SARS-CoV-2 will be contacted via telephone where they will be informed to cease the use of the study medication. A study technician will go to the participant's residence to remove the study medication. The participant will be asked to allow the use of the data collected so far for the safety analysis of halofuginone, for analysis by intention to treat and other analyses.

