## 8.2 Informed Consent Process

Each research participant or their legal representative must provide their written consent in accordance with local requirements, after the nature of the study has been fully explained. The ICF(s) must be signed before any activity related to the study is carried out. The ICF(s) that are used must be approved by the coordinating center and by the REC of the participating centers, and must be in a language that the research participant is able to read and understand. Informed consent must comply with the principles originated in Resolução 466/12 of the National Health Council and with the guidelines of Good Clinical Practices.

Prior to inclusion in the study, the investigator or an authorized member of the research center team must explain to potential research participants or their legal representative the purposes, methods, reasonably anticipated benefits and potential risks of the study, as well as any discomfort that participation in the study may cause. Research participants or their legal representatives will be informed that their

participation is voluntary and that they will be able to withdraw their consent to participate at any time. They will be informed that the choice not to participate will not affect the care they will receive to treat their illness.

Finally, they will be informed that the investigator will keep a record of identification of the research participants and that their records will be accessible by health authorities and the authorized team of the coordinating center without violation of the research participant's confidentiality, at the level permitted by applicable law(s) or regulation(s).

The research participant or his legal representative will have enough time to read the ICF and will have the opportunity to ask questions. After this explanation and before entering the study, consent must be properly registered through the dated personal signature of the research participant or his legal representative and whoever explained it. After obtaining consent, a copy of the ICF must be provided to the research participant. This entire process must be documented in the participant's source document.

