### 8.3 Criteria for discontinuing study participation

The patient will be withdrawn from the study if he withdraws his consent to participate in the study. Details of participant withdrawal must be documented in the source document and eCRF. Upon withdrawal from the study, drug treatments will be determined by the patient's assistant physician. The patient may withdraw his consent to participate in the study for any reason and at any time, without prejudice to the continuity of his medical care.

The request to withdraw consent means that the patient no longer wants to participate in the study, that is, does not want to be evaluated and monitored in the study, perform any procedures related to the study, or be contacted again by the research team. Furthermore, further analysis of previously collected biological materials will not be allowed. In this situation, the study team will only contact the participant to withdraw the study medication. Local investigators must document withdrawal of patient consent and inform the Coordinating Center. Patients who withdraw consent

and discontinue their participation in the study after randomization will not be replaced by other participants.

Randomized patients may also refuse to participate in specific aspects of the study or refuse to continue using the proposed drugs, without withdrawing their consent to participate. In this case, patients should be asked for permission to continue to follow them until the end of the study. Local investigators must make every effort to accommodate the needs of patients to maintain their participation in the study.

It is reinforced that only patients with a positive diagnosis of COVID-19 will be included in the study. However, after randomization (D1), the RT-PCR test will be collected from all participants, necessary for standardizing the test and collection to obtain the viral load of SARS-CoV-2 on the day of inclusion in the study. Although the false-negative rates for rapid tests and RT-PCR that confirmed the diagnosis of COVID-19 in participants (prior to inclusion) are low, it is possible that the participant will have a positive test at the time of inclusion and a negative test. In the first collection of the study (D0). In this circumstance, the participant will no longer receive the proposed treatment, and additional clinical and laboratory data will not be collected.

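### Section 3.10.8 asks rapid-test enrollees later found RT-PCR-negative to permit use of data already collected, so their inclusion in the safety analysis can depend on a choice made after exposure

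*Protocol*

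**What the plan says.** Section 3.10.8 concerns patients enrolled on a rapid genetic or antigen test whose laboratory RT-PCR is negative. They "will be contacted via telephone where they will be informed to cease the use of the study medication", and a technician goes to the home to collect the medication. The section then states: "The participant will be asked to allow the use of the data collected so far for the safety analysis of halofuginone", and in the same sentence "for analysis by intention to treat and other analyses".

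The surrounding text fixes the timing and the consent position:

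- Section 8.2: "The ICF(s) must be signed before any activity related to the study is carried out".
- Section 3.8.1 lists randomisation, the baseline swab and "Dispensing and guiding the use of study medication" for day 1. Table 4 marks treatment from day 1.
- Section 8.3: "after randomization (D1), the RT-PCR test will be collected from all participants".
- Section 8.3 on leaving the study: "The patient will be withdrawn from the study if he withdraws his consent to participate in the study". Its last paragraph describes the same stop of treatment and of data collection after a negative first study swab, and mentions no permission.
- Section 3.10.3 ends clinical and laboratory data collection for patients stopped because of a negative RT-PCR.

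The analysis sets are described in two ways. The synopsis says "The analyses will follow the intention to treat principle". Section 6.1 uses a modified intention-to-treat principle limited to RT-PCR-positive patients.

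**The concern.** A safety analysis should count everyone who was exposed, and an intention-to-treat analysis everyone who was randomised. Neither set should depend on what a patient decides after treatment has begun. The request in 3.10.8 comes when the patient knows how the medication felt. Tolerability may differ between 1 mg, 0.5 mg and placebo, so willingness to agree may differ by arm, and adverse-event or bleeding rates could be distorted in either direction.

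Bleeding is a named safety outcome in section 4.3. Section 3.10.4 reports that 7 of 24 patients in the cited phase I study bled. With about 100 patients planned on halofuginone, single events move the rates. Because collection stops at the negative result, the data covered by the request are the only safety data the trial will hold on these patients.

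**Working it through.** No figure in the protocol depends on this point, so there is none to reproduce. The check is a comparison of the sections, followed by an illustration of scale.

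**1. Is the permission a second one?** Yes. Consent is signed before any study activity (8.2), and the request follows the negative result of a swab that 8.3 places after randomisation.

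**2. Does it usually follow dosing?** Very probably. Drug is dispensed and treatment starts on day 1, and 3.10.8 tells patients to cease use, which presupposes use. The protocol does not state the RT-PCR turnaround time or confirm a first dose for every patient, so this remains an inference.

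**3. Is it consistent with the rest of the protocol?** Not fully. For a patient who withdraws consent outright, 8.3 expressly bars only further analysis of biological material already collected. Section 3.10.8 puts a condition on existing data that the withdrawal section does not state. Section 8.6.1 requires every adverse event to be recorded, with no exception for RT-PCR-negative patients.

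**4. Which analyses are affected?** Read literally, 6.1 limits all analyses to RT-PCR-positive patients, and the data requested in 3.10.8 would have no place in them. Yet 3.10.8 names the safety and intention-to-treat analyses as the purpose of the request, and the synopsis says intention to treat. If 6.1 governs the primary outcome, the request has almost no effect there. For safety, 3.10.8 and 6.1 point in different directions.

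**5. Scale.** The planned size is 50 per arm (section 5). The protocol gives neither the share found RT-PCR-negative (f) nor the share of those who refuse or are not reached (r). Assume f = 0.02 to 0.20 and r = 0.25 to 1.00, with the negatives counted within the 50.

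- Patients lost per arm = 50 × f × r. Lowest: 50 × 0.02 × 0.25 = 0.25. Highest: 50 × 0.20 × 1.00 = 10.
- Upper limit of the exact two-sided 95% interval with zero events = 1 − 0.025^(1/n). For n = 50 it is 7.1%, for n = 49.75 it is 7.2%, and for n = 40 it is 8.8%.
- At the safety interim, 60/3 = 20 per arm. For n = 20 the limit is 16.8%. With 20 × 0.20 × 1.00 = 4 lost, n = 16 and the limit is 20.6%. These patients have no 28-day follow-up, so they may not be among the 60 at all.

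**6. Selective loss.** Assume 3 events in 50, or 6.0%. If two patients who both had an event are lost, the rate becomes 1/48 = 2.1%. If two event-free patients are lost, it becomes 3/48 = 6.3%. Over about 100 halofuginone patients, one lost event changes the rate by about one percentage point.

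**The case against.** The strongest reply is that 3.10.8 only says patients will be asked. A reader might infer that those who refuse or cannot be reached drop out of the safety denominator, but the text states no consequence for either. Section 3.10.10, which assigns the last known clinical status, deals with follow-up contact and does not settle this. The objection stands: exclusion is the natural meaning of asking permission, but it is an inference.

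Several further limits also stand:

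- Failed contact should be uncommon, since a technician visits the home and 3.10.10 provides for several means of contact.
- The request reaches only patients enrolled on a rapid test. Section 3.5 accepts such results when RT-PCR takes more than 24 hours, and 8.3 calls false-negative rates of the pre-inclusion tests low.
- Section 5 describes the 150 patients as RT-PCR-confirmed, so negatives may come on top of the 50 per arm.
- The consent form is not available here. It may already cover retention of data, or the request may reflect an ethics requirement.

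A reader might also infer that the records are lost for good because collection stops. That does not follow: ending future collection does not erase what has been recorded, and 8.6.1 requires adverse events to be recorded in any case.

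What the objection does not remove is the request itself. If the entry consent already covers these data, asking again is unnecessary and still opens a route to selective refusal. An analysis plan cannot repair this, because it cannot use data that a patient has declined to release.

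**Conclusion.** The point holds as a minor one, mainly for the safety analysis. The procedure as written lets use of existing safety data depend on a choice made after randomisation and usually after exposure, and leaves refusal and failed contact undefined.

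The loss of precision is modest. The zero-event upper limit moves from 7.1% to at most 8.8% per arm, and that extreme needs 20% of patients to be RT-PCR-negative and none of them to agree. Both fractions are assumptions. The more relevant risk is selective loss of a few affected patients, whose size and direction cannot be estimated from the protocol.

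A reader might conclude that the primary viral-load comparison is compromised. The protocol does not support that, because 6.1 already leaves RT-PCR-negative patients out. The intention-to-treat part of the request matters only if the synopsis wording is the one that applies.

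**What to change.** Replace the permission request in 3.10.8 with a statement that data collected up to the negative RT-PCR are retained and included in a safety analysis of all randomised patients who took at least one dose, and in any full intention-to-treat analysis, unless the patient withdraws consent under 8.3. Count and report such withdrawals by arm. Put matching wording in the consent form signed at entry, subject to ethics approval.

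Reconcile 3.10.8 with the synopsis (intention to treat) and 6.1 (RT-PCR-positive only), so that the safety set is not limited to RT-PCR-positive patients.

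The cost is a wording change to the protocol and consent form that needs ethics approval, with no added visits, tests or patients. The change does not remove the problem completely: a patient may still withdraw after exposure. That right is kept, but it becomes an exception that is counted rather than a question put to every patient in this group.

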### *3.10.9 Study Helpline*

The study will have a helpline that will be available to answer urgent and non-urgent questions about the management of patients already recruited, as well as questions regarding the eligibility of potential patients for the study.

### *3.10.10 Losses to follow-up*

The study basically consists of out-of-hospital monitoring of patients. Ultimately, obtaining outcome data depends on the contact of the study team with the patient. Strategies to avoid loss to follow-up such as obtaining multiple means of contact (e-mail, phone numbers, addresses) of the participants and an active search for exams and collection of medical records will be implemented.

In case the participant reports adverse events, the researcher in charge of the investigating center will be notified to contact the research participant, so that he is adequately monitored until the resolution of these events.

In situations which there is no success in contact with the patient, the last known clinical status of the patient will be assigned; sensitivity analyzes will be carried out disregarding patients with loss to follow-up in the analysis, and attributing the worst clinically plausible scenario to the losses, corresponding to the imputation in these

subjects of the results observed in the telephone follow-up of the group with the worst clinical results.

### 3.11 Collection, use and storage of biological material

#### 3.11.1 *Blood Tests*

Collections of the following blood laboratory tests will be performed on the day of inclusion in the study (baseline) and on the tenth day: CBC, urea, creatinine, alkaline phosphatase, gamma-GT, aspartate aminotransferase, alanine aminotransferase, direct and indirect bilirubin, C-reactive protein , prothrombin time with INR, activated partial thromboplastin time, fibrinogen, sodium, potassium and a tube for serum analysis of the study drug (will also be collected on the fifth day). Baseline exams will be collected by trained staff from the participating center and 10th day exams will be collected by trained technical staff at the patient's home.

#### 3.11.2 *hCG Urine Test*

The qualitative hCG Urine Test will be performed on baseline in women of childbearing age in order to verify the eligibility criteria

#### 3.11.3 *Nasopharyngeal swab*

All patients in the study will perform nasopharyngeal swab collection to detect the SARS-CoV-2 viral load via RT-PCR on the day of inclusion in the study (baseline), and subsequently on the fifth and tenth days. The baseline swab will be collected by trained staff from the participating center and the exams on the fifth and tenth days will be collected by trained technical staff at the patient home.

Swabs for nasopharynx sample collection should be composed of rayon or dacron. A total of three swabs should be collected, one from each nasal orifice, scraping the meatus, and the other scraping from the palate to the pharynx. The three swabs

should be placed in bottles with 3mL of isotonic medium, preferably DMEM medium with 1% penicillin and streptomycin.

The samples can be stored in a refrigerator (from 2 to 8°C) for 24 hours, or for periods of months in a freezer –20°C or –70°C. As the shipment of the samples will occur within 24 hours, blue-ice can be used to guarantee refrigeration around 4°C.

#### *3.11.4 Locals for processing, storage and performance of laboratory tests*

The biological samples will be sent to the Central Laboratories daily. The Central Laboratories are the Clinical Laboratory of Hospital do Coração, DASA and the Laboratório de Investigações Médicas da Faculdade de Medicina da USP. The biological samples will be processed and analyzed at these laboratories. The routine tests will be performed at the DASA and at the Hospital do Coração; the serum dosage of Halofuginone will be performed at the Laboratório de Investigações Médicas da Faculdade de Medicina da USP and the assessment of SARS-CoV-2 viral load will be performed at Clinical Laboratory of Hospital do Coração. The storage of biological samples will be transient, for enough time to perform all the analyses, as necessary, and they will be destroyed according to Good Laboratory Practices.

All Central Laboratories have adequate infrastructure to develop this research protocol, as refrigerators with strict temperature control, restricted access and monitored by cameras 24 hours a day, 7 days a week. The staff involved on laboratory analyses is trained to perform its activities.

All biological material will be used exclusively for the purposes provided for in this protocol, in accordance with the provisions of Resolução CNS No. 441/2011 and Portaria No. 2.201/2011 and in compliance with the consent obtained from the research participants. There is no intention for future research using the biological samples collected in this study.

### 3.11.5 Clinical data collection

Data will be collected via a digital data collection form (e-CRF) accessed via the internet and developed by the IP-HCor data management team in conjunction with the researcher responsible for the study coordinating center and the responsible statistics team. This tool will be made available via a secure and specialized web platform to support data collection and management, in compliance with current regulations, in accordance with CFR 21 Part 11.

A health professional designated by the participating center will collect data on the day of inclusion of the study (baseline). All professionals who will participate in the study will undergo standardized training for data collection, through electronic conferences, communication via messages and 24 hours a day, every day of the week.

#### Research participants' data collected at Day 1 - baseline (Table 4)

- Demographic data: age, gender
- Baseline data: comorbidities, previous and current use of medications, date of onset of symptoms, clinical symptoms, date of positive SARS-CoV-2 test if available, clinical signs (temperature, heart rate, systolic and diastolic blood pressure, respiratory rate, peripheral oxygen saturation).

**Table 4.** Data from research participants and timeline

|                       | Baseline/
D1 | D2 | D3 | D4 | D5 | D6 | D7 | D8 | D9 | D10 | D14 | D28 |
|-----------------------|-----------------|----|----|----|----|----|----|----|----|-----|-----|-----|
| Screening             | X               |    |    |    |    |    |    |    |    |     |     |     |
| Eligibility           | X               |    |    |    |    |    |    |    |    |     |     |     |
| Informed Consent Form | X               |    |    |    |    |    |    |    |    |     |     |     |
| Randomization         | X               |    |    |    |    |    |    |    |    |     |     |     |
| Interventions         |                 |    |    |    |    |    |    |    |    |     |     |     |

|                                                       |   |   |   |   |    |   |   |   |   |   |   |   |
|-------------------------------------------------------|---|---|---|---|----|---|---|---|---|---|---|---|
| Halofuginone 1mg/day                                  | X | X | X | X | X  | X | X | X | X | X |   |   |
| Halofuginone 0.5mg/day                                | X | X | X | X | X  | X | X | X | X | X |   |   |
| Placebo                                               | X | X | X | X | X  | X | X | X | X | X |   |   |
| Data collection and tests                      |   |   |   |   |    |   |   |   |   |   |   |   |
| Demographic Data                                      | X |   |   |   |    |   |   |   |   |   |   |   |
| Baseline Data                                         | X |   |   |   |    |   |   |   |   |   |   |   |
| Symptoms and signs                                    | X | X | X | X | X  | X | X | X | X | X |   |   |
| RT-PCR SARS-CoV-2                                     | X |   |   |   | X  |   |   |   |   | X |   |   |
| Laboratory tests                                      | X |   |   |   | X* |   |   |   |   | X |   |   |
| Safety Data
(via patients online
questionnaire) | X | X | X | X | X  | X | X | X | X | X |   |   |
| Clinical and safety data via
phone call            |   |   |   |   |    |   |   |   |   |   | X | X |

\* Only serum level of halofuginone

